# Esophagectomy versus definitive chemoradiotherapy for patients with clinical stage N0 and pathological stage T1b esophageal squamous cell carcinoma after endoscopic submucosal dissection: study protocol for a multicenter randomized controlled trial (Ad-ESD Trial)

**DOI:** 10.1186/s13063-020-04461-5

**Published:** 2020-07-01

**Keywords:** Esophageal cancer, Submucosal lesion, Endoscopic submucosal dissection, Definitive chemoradiotherapy, Esophagectomy, Randomized controlled trial

## Abstract

**Background:**

Esophagectomy is still advised as an additional treatment for pathological T1b (pT1b) esophageal squamous cell carcinoma (ESCC) following attempted endoscopic resection (ER). ER followed with definitive chemoradiotherapy (dCRT) has shown increased quality of life as well as comparable oncological outcomes to esophagectomy. However, there is no well-designed phase III trial to compare the two treatments for patients with pT1b ESCC.

**Methods:**

One hundred seventy-six patients with clinical stage N0 (cN0) and pT1b ESCC will be recruited at three centers and randomly assigned to the esophagectomy group or the dCRT group. The clinical lymph node status will be measured by image examination, including computer tomography and positron emission tomography–computed tomography. The pathological tumor status will be diagnosed after endoscopic submucosal dissection (ESD). All patients will be followed up for 60 months after randomization. The primary endpoint is 5-year overall survival. The secondary endpoints are quality of life, related adverse events, 3-year overall survival, and relapse-free survival rates.

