##### Secondary endpoints

QoL is assessed among patients by using the European Organization for Research and Treatment of Cancer Quality of Life Questionnaire C-30 (EORTC QLQ-C30) and EORTC QLQ-OES18 [21, 22]. Patients will be invited to finish the two questionnaires at the day of recruitment and the 1st, 3rd, 6th, 12th, and 24th month after randomization.

The oncological outcomes are 3-year OS and 3- and 5-year relapse-free survival (RFS). RFS is defined as the time from the date of randomization to the day of tumor recurrence, tumor progression, or patients’ death assessed up to 60 months.

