#### Who will be blinded {17a}

Because of the different interventions in the two groups, the thoracic surgeons or radiologists will not be blinded to group allocation. Statistical analysts will be blind to the procedure and the results of randomization, group allocation, and intervention.

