#### Procedure for unblinding if needed {17b}

This trial is an open-label RCT with only statistical analysts being blinded to the procedure and the results of randomization, group allocation, and intervention.

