### Statistical methods

#### Statistical methods for primary and secondary outcomes {20a}

Statistical analyses are performed using SPSS version 20.0 software (SPSS Inc., Chicago, IL, USA). The statistical analysis will be performed in accordance with both the intention-to-treat and the per-protocol principles. Survival will be estimated by Kaplan–Meier methods and analyzed using log-rank test. Continuous variables will be compared using a Student’s *t* test or Wilcoxon rank-sum test as appropriate and represented as the mean ± standard deviation or as median and range. Categorical variables will be compared using Fisher’s exact test or Wilcoxon rank-sum test as appropriate and represented as number of patients and percentage. For the analysis of QoL, parametric or non-parametric statistical methods will be used to assess the results of QLQ-C30 and QLQ-OES18 from pretreatment to 12 months, depending on the data distribution.

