#### Adverse event reporting and harms {22}

Adverse events are defined as any undesirable experience occurring to a subject during the study, regardless of whether they are considered to be related to the treatment procedures. All adverse events reported spontaneously by the subject or observed by the investigator or his or her staff will be recorded during the period of study.

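### The only adverse-event endpoint, in the abstract, is limited to related events in an open-label trial, and the Outcomes section does not list it

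*Protocol article*

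**What the plan says.** The Methods paragraph of the abstract gives the full list of secondary endpoints: "The secondary endpoints are quality of life, related adverse events, 3-year overall survival, and relapse-free survival rates". This is the only place where the article names adverse events as an endpoint, and it restricts them to related ones.

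Outcomes {12} has a subsection headed Secondary endpoints. It opens with "QoL is assessed among patients by using the European Organization for Research and Treatment of Cancer Quality of Life Questionnaire C-30", adds the QLQ-OES18 and the assessment times, and continues "The oncological outcomes are 3-year OS and 3- and 5-year relapse-free survival (RFS", followed by a definition of relapse-free survival. No adverse-event endpoint appears.

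Section {22} defines adverse events "regardless of whether they are considered to be related to the treatment procedures" and says "All adverse events reported spontaneously by the subject or observed by the investigator or his or her staff will be recorded".

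On blinding, {17a} says "the thoracic surgeons or radiologists will not be blinded to group allocation", and {17b} says "This trial is an open-label RCT with only statistical analysts being blinded to the procedure and the results of randomization".

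**The concern.** Two things do not fit. First, the abstract contains an endpoint that the section defining the endpoints lacks. An abstract normally shortens the body. Here every other secondary endpoint reappears in {12} with an instrument, a definition or a time point, and adverse events do not.

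Second, in the only form in which it is stated, the endpoint is filtered by relatedness. Whether an event is caused by treatment is a matter of judgement, and in this trial that judgement would be made at the sites by people who know the arm. The two treatments also differ in kind. Events around an operation and events during or after chemoradiotherapy need not be called related equally readily, even by careful assessors.

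The harms comparison matters here. Background {6a} motivates the trial partly by the morbidity, mortality and loss of quality of life that follow esophagectomy, and hypothesises comparable survival with better quality of life after chemoradiotherapy. If survival proves similar, quality of life and harms will carry much of the treatment choice.

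**Working it through.** The check is mainly a comparison of text; the article gives no adverse-event figure to reproduce.

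**Passages side by side**

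| Place | What it fixes about adverse events |
|---|---|
| Abstract, Methods | Secondary endpoint, related events only |
| {12}, Secondary endpoints | No adverse-event endpoint |
| {22} | All events recorded, related or not; no assessor of relatedness named |
| {17a}, {17b} | Only the statistical analysts are blinded |
| {20a} | Generic rule for categorical data ("Categorical variables will be compared using" Fisher's exact or a rank-sum test); adverse events not named |
| {21b} | Interim safety parameter is peri-treatment mortality |

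1. The abstract and {12} differ on whether a harms endpoint exists. A reader must choose which of them governs.
2. If the abstract governs, the analysed count is a subset of the {22} records, selected by relatedness. Given {17a} and {17b}, selection at the sites is not masked to arm.
3. The abstract and {22} are compatible: related events can be drawn from a record of all events. What {22} shows is that the data for an unfiltered comparison will exist in both arms.
4. The stopping rule in {21b} uses mortality and needs no judgement of relatedness, so it is not touched. It also does not stand in for a morbidity endpoint.

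**What filtering can do**

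Let p be the true proportion of patients with an event, assumed equal in both arms. Let a_S and a_C be the probabilities that such a patient is counted as having a related event after surgery and after chemoradiotherapy. The expected reported difference (surgery minus chemoradiotherapy) is

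p·a_S − p·a_C = p·(a_S − a_C).

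Its sign is the sign of a_S − a_C, and it is zero when attribution is equal. The documents give none of p, a_S or a_C. Purely as an illustration, with every input assumed, take p = 0.30:

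- a_S = 0.95 and a_C = 0.70 to 0.85: 0.30 × 0.95 = 28.5% against 0.30 × 0.70 = 21.0% to 0.30 × 0.85 = 25.5%. The false difference is 3.0 to 7.5 points in favour of chemoradiotherapy.
- The two attribution assumptions exchanged: the same 3.0 to 7.5 points in favour of surgery.
- a_S = a_C: no difference.

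For scale, with 88 patients per arm the standard error of 28.5% minus 21.0% is √(0.285 × 0.715/88 + 0.21 × 0.79/88) = √0.0042 ≈ 6.5 points. So even the largest of these assumed distortions is only a little above one standard error. The illustration shows the mechanism and that it runs both ways; it does not estimate a bias in this trial.

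**The case against.** The strongest reply is that this is a condensed article. It refers to a full protocol that is not shown, adverse events have their own section in {22}, and the Secondary endpoints text does not claim to be exhaustive. On that view the omission is editorial. *Related* is also one undefined adjective: no section describes an assessor or a rule for filtering events. Part of this stands. The absence of a grading scale, a causality method or a time window is not held against the article. But the mismatch lies between two parts of the same article, and the scope that is stated (related events) is a design choice, not a missing detail.

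Three stronger readings are tempting, and the documents do not support them.

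- *That {22} contradicts the abstract.* It does not: recording everything and reporting a related subset are consistent.
- *That no harms would be compared at all.* Section {20b} rules out additional analyses, but its heading concerns analyses such as subgroups, and an endpoint named in the abstract is not an additional analysis. The events are collected in both arms and {20a} offers a usable test.
- *That the comparison must favour chemoradiotherapy.* The direction depends entirely on which arm's events are more readily called related, and the documents say nothing on that.

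**Conclusion.** The point holds as follows. A declared secondary endpoint is missing from the section that defines the endpoints and, as the abstract states it, rests on relatedness judged with the arm known. Attribution may differ between surgery and chemoradiotherapy and could bias the harms comparison either way. The size cannot be estimated from the documents, and the percentages in the illustration should not be cited as an effect in this trial.

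The conclusion rests on two assumptions: that *related* in the abstract carries its usual meaning of judged to be caused by treatment, and that the judgement is made at the sites. If the word was meant loosely, the risk of bias falls away, but the wording in the abstract and {12} still has to be settled. The primary endpoint and the interim mortality rule are unaffected, so this is a matter for the secondary harms comparison only.

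**What to change.** Add one adverse-event endpoint to the Secondary endpoints part of {12}: all-cause adverse events, expressed as the proportion of patients with at least one event, shown by severity where severity is graded, and counted from randomisation over the same period in both arms. Report related events in a descriptive table. Reword the list in the abstract to match. Section {22} can stay as it is, since it already records every event.

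The cost is mostly wording, with two real downsides. All-cause rates will be higher than related-only rates and will include background events in both arms, which may dilute a true difference. A severity threshold on a common scale can be used only if grading is recorded; {22} does not mention it, so it may mean an added data field. The choice of threshold and period can be left to the full protocol or the SAP, provided it is the same in both arms and is fixed before outcome data are compared by arm.

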**Discussion:**

To the best of our knowledge, this is the first phase III randomized controlled trial to compare esophagectomy and dCRT for patients with cN0-pT1b ESCC after ESD. Based on the results of this study, we will show whether dCRT will benefit patients more than esophagectomy, which will contribute more high-quality evidence to the primary salvage treatment for these patients.

**Trial registration:**

ClinicalTrials.gov, NCT04135664. Registered on Aug. 10, 2019.

## Introduction

### Background and rationale {6a}

Esophageal cancer is the seventh most common malignant tumor and ranks sixth in tumor-related mortality worldwide [1]. In terms of the histological subtypes, adenocarcinoma is frequently observed in Europe and the United States whereas squamous cell carcinoma is the predominant form in China [2].

Tumor invasion of the submucosa (T1b) is a watershed in the treatment of esophageal cancer from endoscopy to esophagectomy. Esophagectomy with extended lymph node dissection is recommend as the primary treatment for pT1b esophageal squamous cell carcinoma (ESCC) because of the high incidence of lymph node metastasis [3, 4]. Previous studies showed that patients with pT1b ESCC after esophagectomy had a favorable 5-year survival rate, which was about 70 ~ 73.6% [5, 6]. Although 30 ~ 50% of these patients have a risk of lymph node metastasis, more than half of them are presented with local superficial lesions [7]. In addition, esophagectomy is associated with a higher morbidity and mortality rate as well as decreased quality of life (QoL) [8]. Therefore, preserving the esophagus has always been the ultimate goal of treatment for low-risk submucosal esophageal cancer.

Previous studies have demonstrated that definitive chemoradiotherapy (dCRT) could achieve a survival rate comparable to that of esophagectomy for submucosal esophageal cancer [9]. However, local failure without distant metastasis after dCRT remains a major challenge to achieve long-term survival [10]. Endoscopic resection (ER) has been demonstrated with satisfied control for submucosal esophageal cancer without lymph node metastasis [11]. Therefore, the combination of ER and dCRT conforms to the aim of non-surgical treatment of submucosal esophageal cancer, which can maximize the removal of primary lesions and additional disposition of residual lesions or potential lymph node metastasis [12–14]. The Japan Clinical Oncology Group (JCOG) phase II trial (JCOG0508) was the only prospective clinical study conducted to evaluate the efficiency and safety of combined treatment of ER and CRT for clinical stage I ESCC [15]. The results showed that for patients with pT1b with R0 and pT1a with lymphovascular invasion (+) after ER, the 3-year overall survival (OS) was 90.7% (90% confidence interval 84.0%–94.7%) after prophylactic CRT. They concluded that the combination of ER and selective CRT should be considered as a minimally invasive treatment option for clinical stage I ESCC [16].

Considering the encouraging results of JCOG0508 and other previous studies, we hypothesized that, in comparison with esophagectomy, concurrent dCRT may achieve comparable survival results and better QoL for submucosal esophageal cancer. Therefore, we designed this randomized controlled trial (RCT) to compare the two salvage treatments for pT1b ESCC after ER.

### Objectives {7}

The aim of this trial is to compare esophagectomy versus dCRT for patients with clinical stage N0 and pathological stage T1b ESCC after endoscopic submucosal dissection (ESD).

### Trial design {8}

This study is a multicenter, randomized, open-label, phase III trial. All participants will be allocated to the two intervention groups at 1:1 ratio. The flow chart is illustrated in Fig. 1.

**Fig. 1 Fig1:**
[figure not shown]
Flow chart of the trial

## Methods: Participants, interventions, and outcomes

### Study setting {9}

Patients with cN0-pT1b ESCC after ESD will receive two concurrent salvage treatments. The intervention randomly assigned with either esophagectomy or dCRT will start at about 3 weeks after ESD, followed by a 60-month follow-up period. To achieve the primary endpoint, 176 patients will be recruited from three high-volume centers (>100 cases of esophagectomies) in China (Shanghai Chest Hospital, Zhongshan Hospital, and Changhai Hospital).

### Eligibility criteria {10}

#### Inclusion criteria 

Biopsy proven with ESCC.Clinical N0 stage diagnosed by imaging examinations.Pathological T1b stage confirmed by endoscopic submucosal resection.Age ranges from 18 to 75 years.Primary tumors are located at the intrathoracic esophagus.Eastern Cooperative Oncology Group (ECOG) performance status 0–2.Written informed consent.

#### Exclusion criteria

Prior treatment before endoscopic submucosal resection.Inability to accept any treatment component.Prior intervention (surgery, chemoradiation, etc.) for other primary tumor disease.Positive vertical resection margin.Distant metastasis.Inability to understand the informed consent.

### Who will take informed consent? {26a}

The informed consent document will be obtained from the potential participants or their authorized surrogates after the screening of the inclusion and exclusion criteria. [name] will explain the details of the informed consent document to the participants and their authorized surrogates. The participants will be enrolled in this trial after [name] obtains written permission from participants or their authorized surrogates.

### Additional consent provisions for collection and use of participant data and biological specimens {26b}

On the consent form, participants will be asked whether they agree to the use of their data; otherwise, they could choose to withdraw from the trial. Participants will also be asked for permission for the research team to share relevant data with people from the institutions which are participating in the research or from regulatory authorities (where relevant). This trial does not involve collecting biological specimens for storage.

### Interventions

#### Explanation for the choice of comparators {6b}

The comparator of this trial is esophagectomy. The rate of lymph node metastasis in patients with pathological T1b ESCC was high (20 ~ 50%). According to the current National Comprehensive Cancer Network (NCCN) guidelines of esophageal and gastric cancer, esophagectomy is the primary treatment option for pathological T1b ESCC. The 5-year OS of patients with pT1b ESCC who underwent esophagectomy was 70 ~ 80%. So the comparator we choose for this trial is esophagectomy with lymphadenectomy.

#### Intervention description {11a}

The intervention treatments will be performed by thoracic surgeons or radiologists. Patients who meet the inclusion criteria will be recruited and randomly assigned to two treatment groups.

##### Esophagectomy

Patients will undergo an open, hybrid, or minimally invasive esophagectomy (McKeown or Ivor Lewis) with at least two-field lymphadenectomy. Selection of surgical technique will depend on patient and tumor characteristics as well as local expertise and preference [17–19]. According to the NCCN guidelines [20], the number of dissected lymph nodes should be at least 15, including the lymph nodes at the station of upper para-esophagus, right recurrent laryngeal nerve, middle para-esophagus, lower para-esophagus, left recurrent laryngeal nerve, subcarinal station, left main trachea, right main trachea, para-cardiac, left gastric artery, and lesser curve.

##### Definitive chemoradiotherapy (dCRT)

Radiotherapy will be delivered with photons (6–10 MV) in daily fractions on 5 days per week. Intensity-modulated radiation therapy based on a computed tomography (CT) simulation planning system with 5-mm-thick scan slices throughout the entire neck and thorax and upper abdomen is required.

Target volumes need to be carefully defined.

Gross tumor volume (GTV): The GTV should include the positive margin according to the pathology after ESD.

Clinical target volume (CTV): The CTV is defined as tumor bed and elective lymph node regions. For the proximal third of the esophagus, consider treatment of para-esophageal lymph nodes, bilateral supraclavicular lymph nodes, and mediastinum lymph nodes. For the middle third of the esophagus, consider treatment of para-esophageal lymph nodes. For the distal third of the esophagus, consider para-esophageal, lesser curvature, splenic nodes, and celiac axis nodal regions.

Planning target volume (PTV): The PTV includes PTV-G and PTV-C. Owing to set-up deviation and organ movement, PTV-G is defined as a further 6- to 10-mm expansion to the GTV in all directions and PTV-C is defined as a further 6- to 10-mm expansion to the CTV. The prescribed dose of PTV-G is 6020 cGy (215 cGy/d), PTV-C is 5040 cGy (180 cGy/d), both in 28 fractions.

##### Chemotherapy

The following chemotherapeutic agents were used: Cisplatin was administered at a dose of 70 mg/m^2^ by a slow drip infusion on days 1 and 29; 5-fluorouracil (5-FU) was administered at a dose of 700 mg/m^2^ per d by a continuous infusion for 24 h on days 1–4 and 29–32.

##### Criteria for discontinuing or modifying allocated interventions {11b}

Allocated interventions will not be modified as a rule, except for participants who cannot finish chemoradiation because of severe adverse events.

#### Strategies to improve adherence to interventions {11c}

Because this is a surgical RCT, there will be no further strategy to improve adherence to interventions.

#### Relevant concomitant care permitted or prohibited during the trial {11d}

In this trial, implementing psychological instruction will not require alteration to usual care pathways (including use of any medication) and these will continue for both trial arms.

#### Provisions for post-trial care {30}

All participants will be followed up over a period of 60 months or until death.

#### Outcomes {12}

##### Primary endpoint

The primary endpoint is 5-year OS in all randomly assigned patients. OS is defined as the time from the date of randomization to the day of last follow-up or death.

##### Secondary endpoints

QoL is assessed among patients by using the European Organization for Research and Treatment of Cancer Quality of Life Questionnaire C-30 (EORTC QLQ-C30) and EORTC QLQ-OES18 [21, 22]. Patients will be invited to finish the two questionnaires at the day of recruitment and the 1st, 3rd, 6th, 12th, and 24th month after randomization.

The oncological outcomes are 3-year OS and 3- and 5-year relapse-free survival (RFS). RFS is defined as the time from the date of randomization to the day of tumor recurrence, tumor progression, or patients’ death assessed up to 60 months.

### Participant timeline {13}

The time schedule of enrolment, interventions, assessments, and visits for participants is presented in the following schematic diagram.

### Sample size {14}

According to previous studies, the 5-year OS of patients with pT1b ESCC who underwent esophagectomy was 70 ~ 80% [23] whereas the rate was about 90% in patients who received ER plus chemoradiation [16]. We assumed that the 5-year OS rates were 75% in the esophagectomy group and 90% in the dCRT group. The proportion dropping out of the study is considered to be 5%. Therefore, a sample size of 88 patients in each group is required at a significance level of 5% and a power of 80%.

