## Discussion

In an increasing numbers of patients, superficial lesions are treated primary with ER after receiving lymph node and distant metastasis evaluation. However, the treatment choice will face a dilemma between esophagectomy and dCRT when the pathology of ER specimen reveals submucosal invasion, which is an increasingly common clinical problem [24]. In the past, the selection was based on the preferences of patient and doctor. Although previous retrospective studies have confirmed that adjuvant chemotherapy or surgery can achieve comparable long-term survival outcomes, small sample size and low proportion of pT1b patients reduced the credibility of evidence [14, 16]. The present study is the first prospective randomized controlled clinical trial to compare the salvage esophagectomy and dCRT for patients with cN0-pT1b ESCC after ESD. Our results will provide high-level evidence to establish an appropriate treatment strategy for these patients.

Superficial esophageal cancer is defined as tumor invaded into mucosal and submucosal lesion. In the retrospective studies, tumor invaded into muscular mucosal (M3) and submucosal (SM) layers are usually treated in the same way because of the high rate of lymph node metastasis [25]. However, we selected T1b as the study subject and excluded M3 patients in this trial, which is based mainly on the following considerations. First, it is difficult to be recruited since the majority of patients with mucosal myometrium after R0 resection in China will choose surveillance. Second, in this trial, we set very strict clinical evaluation criteria for lymph node status, which greatly reduced the probability of occurrence of high-risk M3, so there is no need for adjuvant therapy. Therefore, the T1b patients after ESD were selected as the study subjects.

In this trial design, we did not exclude patients with a positive lateral resection margin. Previous studies have confirmed that the tumor invasion within the submucosa can be well controlled by radiotherapy, and so for the residual lesions in the lateral resection margin after ESD, subsequent adjuvant chemoradiotherapy or surgery is sufficient to obtain local radical treatment [26]. Therefore, those patients do not need to be excluded, which was also consistent with the JCOG0508 study [16]. However, because the tumor has invaded into the muscular layer (T2), patients with a positive vertical resection margin will not be recruited.

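### The 90% 5-year survival assumed for dCRT is supported in the protocol only by a 3-year rate; if deaths continue after year 3, power is well below 80%

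*Protocol article*

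**What the plan says.** The Sample size section takes the comparator from earlier reports: "the 5-year OS of patients with pT1b ESCC who underwent esophagectomy was 70 ~ 80% [23"]. The same sentence goes on to the experimental arm: "whereas the rate was about 90% in patients who received ER plus chemoradiation [16"]. Read in sequence, both figures are 5-year rates, and the next sentence uses them so: "We assumed that the 5-year OS rates were 75% in the esophagectomy group and 90% in the dCRT group". With 5% dropout, the section concludes that "a sample size of 88 patients in each group is required at a significance level of 5% and a power of 80" per cent.

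The Background and rationale section describes the study behind that citation. The survival result it gives is: "the 3-year overall survival (OS) was 90.7% (90% confidence interval 84.0%–94.7%) after prophylactic CRT". The group it refers to is described as "for patients with pT1b with R0 and pT1a with lymphovascular invasion (+) after ER".

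The primary endpoint is 5-year overall survival, and the Statistical methods section names Kaplan–Meier estimation and the log-rank test. The sample size formula and the sidedness of the test are not stated.

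**The concern.** The two sections attach different time points to what looks like the same result from the same reference. If the 90% is in fact the 3-year figure, the planned difference compares one arm at 3 years with the other at 5 years, and the true 5-year difference is smaller by whatever mortality occurs in years 4 and 5.

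The whole sample size rests on this input. The Background also hypothesises that dCRT gives comparable survival with better quality of life, while the sample size is set for a 15-point superiority. If power is far below 80%, a non-significant log-rank test is a likely result even when dCRT is better by 10 points. Given the stated hypothesis, such a result could easily be misread as evidence of comparable survival.

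The populations differ too. The 90.7% is reported for pT1b with R0 resection plus some pT1a, whereas this trial takes pT1b only and, in the words of its Discussion, "we did not exclude patients with a positive lateral resection margin". The document gives no figure from which to size this difference, so the calculations below ignore it.

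**Working it through.** **Inputs.** From Sample size: 75% and 90% at 5 years, 5% significance, 80% power, 5% dropout, 88 per arm. From Background: 90.7% at 3 years, 90% confidence interval 84.0% to 94.7%. Assumptions added here: the hazard shape after year 3, the sidedness, and follow-up to 60 months. Each calculation uses n = 88 per arm, and n = 88 × 0.95 = 83.6 after dropout.

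**Formulas.**
- Two proportions: power = Φ{[|p1 − p2|√n − z√(2p̄(1 − p̄))] / √[p1(1 − p1) + p2(1 − p2)]}.
- Log-rank (Schoenfeld): power = Φ{|ln HR|√D/2 − z}, with HR = ln S2/ln S1 and D = n(2 − S1 − S2).
- z = 1.960 two-sided, 1.645 one-sided.

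**Step 1: the plan's own 88.** For 75% versus 90%, HR = ln 0.90/ln 0.75 = 0.366.
- One-sided Freedman log-rank: 29 events; 29/0.35 = 82.9 per arm; 82.9/0.95 = 87.2, rounded up to 88. This matches.
- Two-sided Schoenfeld log-rank, 88 per arm, no dropout loss: 79.6% power, also close. With 83.6 per arm: 77.5%.
- Two-sided two proportions: 100 per arm, 106 with dropout. Power is 74.9% at 88 and 72.7% at 83.6.

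So 88 can be reproduced, but at the unchanged 75% versus 90% two-sided power is about 73–80%.

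**Step 2: what 90% at 5 years requires.** Annual hazard in years 1–3: −ln(0.907)/3 = 0.0325. Annual hazard in years 4–5 needed to reach 90%: ln(0.907/0.900)/2 = 0.0039. The hazard would have to fall about 8.4-fold.

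**Step 3: the 5-year rate under other hazard shapes.**
- Constant: 0.907^(5/3) = 0.850.
- Halved after year 3: 0.907 × exp(−0.5 × 0.0325 × 2) = 0.878.
- Quartered after year 3: 0.907 × exp(−0.25 × 0.0325 × 2) = 0.892.

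**Step 4: power against 75%.** For constant hazard, HR = ln 0.850/ln 0.75 = 0.566 and D = 88 × (0.25 + 0.150) = 35.2, so log-rank power = Φ(0.570 × 5.93/2 − 1.96) = 39.4%. The other cases follow in the same way; each range spans both tests and both values of n. Where the hazard changes after year 3, the log-rank figure is an approximation from the 5-year rates.

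| Hazard after year 3 | 5-year dCRT | Two-sided power |
|---|---|---|
| Constant | 85.0% | 36–39% |
| Halved | 87.8% | 57–62% |
| Quartered | 89.2% | 67–74% |
| No deaths | 90.7% | 77–84% |

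One-sided, the constant-hazard case gives 49–52%. A simulated two-sided log-rank test (88 per arm, exponential survival, 60 months, 5% dropout) gives 37.8% for 75% versus 85%, in agreement.

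**Step 5: the control range in the protocol.** Two-sided power, in per cent, over both tests and both values of n:

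| Control | dCRT 85% | dCRT 88% | dCRT 90% |
|---|---|---|---|
| 70% | 64.4–69.6 | 82.1–87.7 | 90.6–95.1 |
| 75% | 36.5–39.5 | 58.2–63.8 | 72.7–79.6 |
| 80% | 13.3–14.0 | 29.0–31.5 | 44.0–48.7 |

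**Step 6: detectable difference.** At 75% control, the simulated log-rank power is 78.0% at 90.5% and 81.3% at 91%. So 80% power needs about 91%, a difference of about 16 points.

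**The case against.** A reader might infer that power is 38% on the protocol's own figures. The documents do not support that. The protocol never states 85%; that value needs a constant hazard, and 38% also needs a two-sided test. The protocol gives neither, and the convention that reproduces 88 with the stated dropout is one-sided, under which the constant-hazard power is about 50%.

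A reader might also infer that 90% simply is the source's 3-year rate. That cannot be confirmed. The cited paper is not at hand and may contain a 5-year rate, and the Discussion says the calculation also drew on the investigators' clinical observation. What the document does show is that 90% at 5 years is not supported by the one result it reports from that paper.

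The source's uncertainty is wide as well. Under constant hazard its confidence limits convert to 0.840^(5/3) = 74.8% and 0.947^(5/3) = 91.3%, and two-sided log-rank power at 88 per arm then runs from about 3% to about 88%. So 90% lies inside the range, although well above its centre.

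Follow-up could also be longer. One section says at least 60 months. At 80 patients a year from November 2019 with completion in December 2027, mean follow-up would be about 84 months. Then 75% versus 85% at 5 years yields about 88 × [(1 − 0.75^1.4) + (1 − 0.85^1.4)] = 47 events and roughly 50% two-sided power before dropout.

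Finally, not all of the gap below 80% comes from the time point: Step 1 shows that part comes from the choice of test and the handling of dropout.

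These points stand, and they are why the result is given as a conditional range. They do not restore 80%: with a two-sided test and 60 months of follow-up, that level is reached only if deaths almost cease after year 3.

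**Conclusion.** The point holds as a conditional one. The planning value of 90% at 5 years has no support in the protocol other than a 3-year rate of 90.7%, so the 15-point effect appears to mix time points. If the hazard is constant, power at 75% control is about 36–39% two-sided, or 49–52% one-sided. If it halves after year 3, two-sided power is about 57–62%. These figures assume 75% control survival, follow-up to 60 months and 83.6 to 88 evaluable patients per arm. Separately, the stated 80% is at the top of what a two-sided test gives at 75% versus 90%. The direction is secure unless a 5-year rate near 90% can be produced; the exact power is not.

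**What to change.** In the Sample size section:

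1. Cite a 5-year rate for dCRT that the source supports, or show the conversion from 3 to 5 years and the hazard assumption behind it.
2. State the test and its sidedness in place of the bare "at a significance level of 5% and a power of 80" per cent, and say how dropout enters the calculation.
3. Restate the power of 176 patients as a short table over control rates of 70–80% and dCRT rates of 85–90%, with the difference detectable at 80% power (about 16 points, two-sided, at 75% control).
4. State that a non-significant result will not be read as showing comparable survival.

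This changes wording only. The cost is a less favourable stated power, and no extra patients are needed. If the sponsor would rather keep 80% power at 75% versus 85%, a two-sided two-proportion calculation gives 251 per arm, or 251/0.95, rounded up to 265, with dropout. That would be a different trial and is not what is asked for here.
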